# A multi-level intervention in subsidized housing sites to increase fruit and vegetable access and intake: Rationale, design and methods of the ‘Live Well, Viva Bien’ cluster randomized trial

**DOI:** 10.1186/s12889-016-3141-7

**Published:** 2016-06-28

**Keywords:** Diet, Food access, Fruit and vegetable, Farmer’s market, Mobile market, Nutrition education: Low income

## Abstract

**Background:**

Adequate fruit and vegetable (F&V) intake is important for disease prevention. Yet, most Americans, especially low-income and racial/ethnic minorities, do not eat adequate amounts. These disparities are partly attributable to food environments in low-income neighborhoods where residents often have limited access to affordable, healthful food and easy access to inexpensive, unhealthful foods. Increasing access to affordable healthful food in underserved neighborhoods through mobile markets is a promising, year-round strategy for improving dietary behaviors and reducing F&V intake disparities. However, to date, there have been no randomized controlled trials studying their effectiveness. The objective of the ‘Live Well, Viva Bien’ (LWVB) cluster randomized controlled trial is to evaluate the efficacy of a multicomponent mobile market intervention at increasing F&V intake among residents of subsidized housing complexes.

**Methods/Design:**

One housing complex served as a pilot site for the intervention group and the remaining 14 demographically-matched sites were randomized into either the intervention or control group. The intervention group received bimonthly, discount, mobile, fresh F&V markets in conjunction with a nutrition education intervention (two F&V campaigns, newsletters, DVDs and cooking demonstrations) for 12 months. The control group received physical activity and stress reduction interventions. Outcome measures include F&V intake (measured by two validated F&V screeners at baseline, six-month and twelve-months) along with potential psychosocial mediating variables. Extensive quantitative and qualitative process evaluation was also conducted throughout the study.

**Discussion:**

Modifying neighborhood food environments in ways that increase access to affordable, healthful food is a promising strategy for improving dietary behaviors among low-income, racial and ethnic minority groups at increased risk for obesity and other food-related chronic diseases. Discount, mobile F&V markets address all the major barriers to eating more F&V (high cost, poor quality, limited access and limited time to shop and cook) and provide a year-round solution to limited access to healthful food in low-income neighborhoods. LWVB is the first randomized controlled trial evaluating the effectiveness of mobile markets at increasing F&V intake. If proven efficacious at increasing F&V consumption, LWVB could be disseminated widely to neighborhoods that have low access to fresh F&V.

**Trials registration:**

Clinicatrials.gov registration number: NCT02669472 First Received: January 19, 2016.

**Electronic supplementary material:**

The online version of this article (doi:10.1186/s12889-016-3141-7) contains supplementary material, which is available to authorized users.

## Background

Eating ample amounts of fruits and vegetables (F&V) is associated with a lower risk for many chronic diseases [1–8] and may also help with weight management [2, 9–11]. The Dietary Guidelines for Americans recommend a daily intake of 3 ½ to 5 cups of F&V [12] Yet, most U.S. adults fall short of these recommendations, [13–15] with low income and some racial/ethnic minority groups even less likely to eat the recommended amount of F&V [16–25].

These disparities are partly attributable to the food environments in low-socioeconomic status (SES) and racial/ethnic minority neighborhoods, where residents often have limited access to affordable, healthful, high quality food and easy access to inexpensive, unhealthful food [19, 22, 23, 25–29]. Retail food outlets in these neighborhoods are generally less likely to stock healthful foods, more likely to offer lower quality produce, and more likely to have higher prices than stores in higher-income or predominantly Non-Hispanic white neighborhoods [30–41].

These findings support previous quantitative and qualitative studies, which identified the major barriers to eating more F&V as high cost, poor quality and limited access [20, 25, 42–46]. Other documented barriers to eating more F&V are hectic lifestyles (leaving little time for shopping and cooking), food preferences, negative attitudes and perceived norms regarding healthy eating, and lack of knowledge, skills, self-efficacy and social support [47–56]. Although individuals’ dietary choices are personal decisions, they are made within a complex mix of social and environmental influences that can make healthier choices more or less easy, accessible, and affordable [57–59]. Thus, altering environmental and social influences on eating behaviors is a promising strategy that may be more generalizable, cost-effective, and sustainable than individual or group behavior change interventions [34, 60–62].

Farmer’s markets and mobile F&V markets have emerged as an innovative approach for increasing access to healthful food [49, 63]. Although such markets demonstrate potential for improving dietary intake, there have been no randomized trials studying their efficacy to date. Additionally, while environmental interventions such as mobile markets may improve F&V intake by increasing access, a multi-level approach that also delivers behavioral interventions to increase motivation and skills and to decrease personal barriers to increasing F&V intake may be the most effective approach [64, 65]. The work of Dibsdall et al., found that for low SES adults, access and affordability were only two of the problems surrounding low F&V consumption and that personal determinants needed to be addressed as well [66]. Thus, research is needed on practical, cost-effective interventions that not only improve F&V access and affordability but also change personal determinants such as knowledge, skills, perceived barriers, attitudes, self efficacy and perceived social support [16, 59]. The purpose of this paper is to describe the intervention development, protocols and measures used in the ‘Live Well, Viva Bien’ (LWVB) research study.

LWVB is a cluster randomized controlled trial in 15 subsidized housing complexes designed to evaluate the efficacy of a multicomponent intervention that includes discount, mobile fresh F&V markets--*‘Fresh To You’(FTY)* —in conjunction with a nutrition education intervention. The primary aims of this study are to: 1) Conduct formative research with residents living in subsidized housing projects to inform the multi-level intervention and; 2) Implement a cluster randomized trial to study the efficacy of the FTY markets combined with the educational/motivational interventions at increasing F&V access, availability, and consumption compared to a Comparison intervention (attention placebo).

In addressing the aforementioned specific aims, we also have the opportunity to examine mechanisms involved in the delivery and receipt of programming and the potential causal effects of the intervention. To that end, we are addressing the following secondary aims: 1) To include extensive implementation process evaluation to determine costs, reach, fidelity and dose and the relationship of these variables with evaluation outcomes; and to 2) Use a mediating variable framework to examine relationships among important psychosocial factors/determinants with changes in F&V consumption.

## Methods

### Overview of study design

All study activities occur at housing sites in Providence County, Rhode Island. Pre-intervention focus groups were conducted with housing complex residents (from non-study sites) to inform intervention development. A total of 15 subsidized housing complexes were recruited into the evaluation cohort. One smaller housing complex served as a pilot site for the intervention group and the remaining fourteen demographically-matched sites were randomized into either the intervention or control group. Adult residents from each housing site were recruited for the evaluation cohort prior to randomization. The multicomponent intervention lasts one year and includes baseline, 6 and 12 month follow-up surveys as well as extensive quantitative and qualitative process evaluation throughout the course of the study. Participants are given a $30 gift card incentive upon completion of each of the three surveys ($90 total). All study protocols were approved by the Brown University Institutional Review Board and all participants provided verbal informed consent. A detailed description of the intervention and evaluation follows.

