### Intervention components

#### ‘Fresh To You’(FTY) discount, fresh fruit and vegetable markets

The intervention sites receive regularly-scheduled, discount, fresh F&V markets for one year. These FTY markets are not farmer’s markets, but rather mobile markets selling both local and non-local produce on a year-round basis at prices at or below local supermarket prices [74]. For the current study, the original plan to bring the markets to each housing complex on a weekly basis changed as we learned through the pilot that most residents only shopped at the markets the first two weeks of the month, consistent with disbursement of Supplemental Nutrition Asssistance Program (SNAP) benefits. Therefore, at the next seven (7) intervention sites, markets were only scheduled during the first two weeks of each month.

Prior to starting the markets, Brown research staff met with the designated site contacts, who helped determine the best times and locations for the markets. On a mutually agreed upon schedule, our produce distributor brings FTY markets carrying between 50 to 70 different produce items, including staples (e.g., potatoes, onions, carrots, celery, tomatoes and bananas); seasonal items (e.g.,clementines in the winter and peaches and blueberries in the summer); culturally desired ethnic produce items (e.g., plaintains, yucca and mangoes) and exotic produce (e.g. Asian pears and purple eggplant) to introduce new F&V to residents.

The majority of the FTY markets at the senior and disabled housing complexes are held indoors as it is difficult for many of these residents to get outside to shop. Markets are also held indoors at family housing complexes during inclement weather. F&V are arranged in bins on the tables in a central location. A check-out station is set up on a separate table that includes a scale for produce weighing and a Point-of-Sale (POS) system that serves as a cash register and a data collection and reporting unit.

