### Sample size considerations

The original sample size projections showed that ending the study with 75 participants in each of 16 housing complex sites (8 sites per condition) using reasonable estimates of the intraclass correlation (0.01) and Standard Deviation 2.5 (based on our previous studies), we would be able to detect an effect size of 0.50 cups (based on F&V Screener change scores) between experimental groups with 80 % power. We originally planned to recruit 16 sites but dropped our sample size slightly (7 sites in each condition and 1 pilot site = 15 sites) because of large budget cuts from NCI at the beginning of the funding period. We anticipated retention at 75 % or greater of the original sample so aimed to enroll an average of at least 107 participants at each of the 15 housing sites.

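### The non-randomised pilot site is counted in the 15-site trial, evaluation cohort and enrolment target, and nothing keeps it out of the efficacy comparison

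*Protocol article*

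**What the plan says.** Two descriptions of the trial stand side by side in the protocol article.

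- **Fourteen randomised.** Overview of study design: "One smaller housing complex served as a pilot site for the intervention group and the remaining fourteen demographically-matched sites were randomized". The Abstract says the same. Under Randomization, allocation is made within each matched pair once baseline surveys at that pair are complete. Fourteen sites make seven such pairs and leave the pilot without one.
- **Fifteen in the trial.** Background: "LWVB is a cluster randomized controlled trial in 15 subsidized housing complexes". Overview of study design: "A total of 15 subsidized housing complexes were recruited into the evaluation cohort". Sample size considerations gives the reduced design as "7 sites in each condition and 1 pilot site = 15 sites" and says the team "aimed to enroll an average of at least 107 participants at each of the 15 housing sites".

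The section on the Fresh To You markets places the pilot among the intervention sites. It says that "the original plan to bring the markets to each housing complex on a weekly basis changed as we learned through the pilot", and continues: "Therefore, at the next seven (7) intervention sites, markets were only scheduled during the first two weeks of each month". The pilot is thus the first of eight intervention sites. The Comparison/control intervention section gives seven comparison sites.

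Data analysis specifies a mixed model that allows for clustering by housing site. It mentions neither exclusion nor separate handling of the pilot.

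**The concern.** A cluster randomised trial takes its validity from the random assignment of clusters. A site placed in one arm by decision has no such protection, and here it differs from the others in ways the article itself reports. It is smaller, although number of units was a matching factor. It has no control partner. It also seems to have operated before the market schedule was changed. The Overview's statement that residents at each site were recruited before randomisation cannot apply to a site that was never randomised.

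If this site is pooled with the seven randomised intervention sites, the estimate is no longer a purely randomised one. That matters because the Discussion presents the study as the first randomised evidence on mobile markets and expects it to support funding decisions. With so few clusters, one of them is not negligible.

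**Working it through.** **Inputs.** From Sample size considerations: SD 2.5 cups, intraclass correlation (ICC) 0.01, target difference 0.50 cups, 80 % power, 75 completers per site, 8 sites per condition originally, enrolment of 107 per site, retention of 75 % or more. Alpha and sidedness are not stated, so 5 % is assumed and both one-sided and two-sided results are shown.

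**Formulas.** Design effect = 1 + (m − 1) × ICC, with m completers per site. SE = SD × √[design effect × (1/(k₁m) + 1/(k₂m))], with k₁ and k₂ sites per arm. Normal power = Φ(0.50/SE − critical value). The t version uses a noncentral t on k₁ + k₂ − 2 degrees of freedom.

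**Step 1: the plan's own figure, and the effect of the pilot on power.** With m = 75, the design effect is 1 + 74 × 0.01 = 1.74.

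| Sites | SE | Power, two-sided normal | Power, two-sided t | Power, one-sided t |
|---|---|---|---|---|
| 8 v 8 (original plan) | 0.1904 | 74.7 % | 68.5 % | 80.3 % |
| 8 v 7 (pilot counted) | 0.1971 | 71.8 % | 65.1 % | 77.5 % |
| 7 v 7 (randomised only) | 0.2035 | 69.0 % | 61.7 % | 74.9 % |

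The stated 80 % is matched by the one-sided 5 % t test for 8 v 8. The two-sided versions fall short of it. On every version the pilot adds about 3 points (71.8 − 69.0 = 2.8; 65.1 − 61.7 = 3.4; 77.5 − 74.9 = 2.6). For 7 v 7, the difference detectable with 80 % power (two-sided) is 0.570 cups by the normal formula and 0.621 by the t formula.

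**Step 2: precision at the enrolment target.** Completers per site: 107 × 0.75 = 80.25. Design effect: 1 + 79.25 × 0.01 = 1.7925.

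- 8 v 7: SE = 2.5 × √[1.7925 × (1/642 + 1/561.75)] = 0.193
- 7 v 7: SE = 2.5 × √[1.7925 × (2/561.75)] = 0.200
- Ratio 0.1997/0.1934 = 1.033, so about 3 % wider

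**Step 3: possible bias if the pilot is pooled.** With equal site weights, the pilot holds 1/8 of the intervention-arm mean. It is smaller, so in a participant-level model its weight is probably below that. Bias = weight × (pilot's mean change − mean change expected at a randomised intervention site). The documents do not give that shift.

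- One scale comes from the plan's inputs: between-site SD = √0.01 × 2.5 = 0.25 cups. A shift of this size gives 0.25/8 = 0.031 cups, or 6 % of the 0.50-cup target and 0.16 of the 8 v 7 SE.
- An assumed shift of 0.5 cups gives 0.5/8 = 0.0625 cups, or 12.5 % of the target and 0.32 of the SE.

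**Step 4: enrolment.** 15 × 107 = 1605 in total, of which 14 × 107 = 1498 are at randomised sites.

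**The case against.** The strongest reply is that no sentence places the pilot in the primary contrast. Data analysis is one paragraph in a journal article and defines no analysis set. That definition may sit in a full protocol or statistical analysis plan that is not shown. An evaluation cohort could simply mean the sites whose residents are surveyed, and pilot residents could serve the process evaluation only. The article is also open about the pilot not being randomised. This stands, and it makes the bias conditional on pooling. It does not remove the point: a randomised trial in 15 complexes is contradicted by the article's own account, and the 15-site statements invite pooling.

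A reader might go further in four ways that the documents do not support.

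- **That the sample size calculation treats the pilot as an eighth intervention cluster.** Sample size considerations lists it apart from the seven sites per condition and gives no power figure for 15 sites, so no stated power is inflated by it. The count of eight comes from the Overview and the market section together.
- **That pilot residents were recruited knowing their arm, or that the site had weekly markets throughout.** Both are inferences. The article does not say when the site was designated, what residents were told, or how long any weekly schedule lasted there.
- **That the bias could reach a quarter of the target.** This needs a 1.0-cup shift, which is four between-site SDs on the plan's inputs and has no source.
- **That the planned analysis cannot accommodate the site.** A strictly paired analysis could not, but the article specifies a mixed model with a site effect, which can hold 15 sites.

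**Conclusion.** The point holds in a conditional form. The pilot was assigned rather than randomised, is smaller and unpaired, and probably ran under the earlier market plan. The article still counts it in the trial label, the evaluation cohort, the intervention group and the enrolment target, without separating it in the analysis. Followed as written, the text leads to an 8 v 7 comparison with one non-randomised cluster.

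The likely size is modest: about 0.03 to 0.06 cups for shifts of 0.25 to 0.5 cups, direction unknown. This rests on a weight of 1/8 as an upper bound and on an assumed shift. It would be too strong to say that the randomised comparison is already broken, because pooling is the natural reading and not a stated decision. The case for change is one of validity. The gain in precision from including the site is too small to justify leaving the matter open.

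**What to change.** - In Data analysis, state that the primary efficacy analysis uses only the 14 randomised sites.
- Report the pilot site descriptively, and add it in one labelled sensitivity analysis.
- In the Background, describe the trial as 14 randomised sites plus one non-randomised pilot. Make the Overview's statements on the evaluation cohort and on recruitment before randomisation consistent with that.
- In Sample size considerations, restate sample size and power for 7 v 7 randomised sites, giving the alpha and sidedness used, and show pilot enrolment separately.

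The cost is mainly wording. Compared with pooling the pilot, the SE rises from 0.193 to 0.200 (about 3 %) at 80.25 completers per site, or roughly 3 points of power for 0.50 cups. The pilot data are still collected and reported.

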### Recruitment of housing sites

A recruitment brochure delineating the details of the study and the benefits for participating sites was distributed to subsidized housing complexes in Providence County, Rhode Island that had at least 190 units. Meetings were held with housing complex administrators and staff at potential sites to discuss the study and its benefits, as well as to ascertain their interest in participating. A housing authority official from each interested housing site signed a Memorandum of Agreement, which delineated the responsibilities of the researchers and the participating housing authority. A Resident Assistant from each housing site was hired to assist with recruitment and intervention activities.

### Eligibility criteria for housing sites

In order to participate in the study, the housing complex needed to have: at least 190 units; a relatively low turnover rate (<20 %); a community room or center where surveys, markets and other intervention activities could occur; a willingness to be randomized into one of the two experimental conditions, support the study activities for the duration of the study and help Brown research staff recruit and hire an on-site Resident Assistant. In addition, at least 90 % of the residents needed to be able to speak and read either English or Spanish.

Housing sites were recruited into the study in pairs, matched by number of units, type of site (family or elderly/disabled) and race/ethnicity. The first seven participating sites were Providence Housing Authority sites. The next four sites were Pawtucket Housing Authority Sites and the last four sites were Woonsocket Housing Authority Sites. Nine sites were elderly/disabled housing sites and six were family sites.

### Recruitment of study participants

Participant recruitment at each housing complex lasted for approximately one to three months and began with an on-site recruitment event in the housing complex community room. In advance of an event, Brown research staff and the Resident Assistant displayed posters and door hangers throughout the complex to advertise the recruitment event, study details, and a toll-free number to call with any questions.

On the day of the recruitment event, Brown research staff set up tables in the housing complex community room. An Excel sheet log that included a list of all room numbers in the housing complex was given to the Resident Assistant, who was seated at a table at the entrance to the community room. She greeted residents, verified that they lived in the housing complex and checked off their room number on the Excel sheet. Residents were then escorted to the tables where Brown’s bilingual research staff further screened them to ensure that they met all of the eligibility criteria. If found to be eligible and interested in participating, residents consented to participate and were enrolled in the study.

### Eligibility criteria of participants

To participate in the evaluation study, participants needed to: be 18 years of age or older; live in the housing complex as a full-time resident; shop for their household’s food at least half of the time, not have any major medical conditions that would prevent them from participating in study activities or events; not be planning to move in the next year; be able to read and understand either English or Spanish; and have access to a Digital Video Disk (DVD) player (or computer that could play DVDs). If housing residents were not eligible or did not choose to be in the evaluation study, they were still invited to participate in the intervention activities.

### Baseline surveys

Baseline surveys were either conducted by Brown research staff, either in-person at the housing complex, or by phone via computer-assisted telephone interviewing. All baseline data that was collected in person was first reviewed for completeness by Brown data clerks and then entered into the online computer database.

